## Abstract

**Background:**

Acute respiratory failure (ARF) is a common and life-threatening medical emergency. Standard prehospital management involves controlled oxygen therapy and disease-specific ancillary treatments. Continuous positive airway pressure (CPAP) is a potentially beneficial alternative treatment that could be delivered by emergency medical services. However, it is uncertain whether this treatment could work effectively in United Kingdom National Health Service (NHS) ambulance services and if it represents value for money.

**Methods:**

An individual patient randomised controlled external pilot trial will be conducted comparing prehospital CPAP to standard oxygen therapy for ARF. Adults presenting to ambulance service clinicians will be eligible if they have respiratory distress with peripheral oxygen saturation below British Thoracic Society (BTS) target levels, despite titrated supplemental oxygen. Enrolled patients will be allocated (1:1 simple randomisation) to prehospital CPAP (O_two system) or standard oxygen therapy using identical sealed boxes. Feasibility outcomes will include incidence of recruited eligible patients, number of erroneously recruited patients and proportion of cases adhering to allocation schedule and treatment, followed up at 30 days and with complete data collection. Effectiveness outcomes will comprise survival at 30 days (definitive trial primary end point), endotracheal intubation, admission to critical care, length of hospital stay, visual analogue scale (VAS) dyspnoea score, EQ-5D-5L and health care resource use at 30 days. The cost-effectiveness of CPAP, and of conducting a definitive trial, will be evaluated by updating an existing economic model. The trial aims to recruit 120 patients over 12 months from four regional ambulance hubs within the West Midlands Ambulance Service (WMAS). This sample size will allow estimation of feasibility outcomes with a precision of < 5%. Feasibility and effectiveness outcomes will be reported descriptively for the whole trial population, and each trial arm, together with their 95% confidence intervals.

**Discussion:**

This study will determine if it is feasible, acceptable and cost-effective to undertake a full-scale trial comparing CPAP and standard oxygen treatment, delivered by ambulance service clinicians for ARF. This will inform NHS practice and prevent inappropriate prehospital CPAP adoption on the basis of limited evidence and at a potentially substantial cost.

**Trial registration:**

ISRCTN12048261. Registered on 30 August 2017. http://www.isrctn.com/ISRCTN12048261

## Background

Acute respiratory failure (ARF) is a common medical emergency which occurs when disease of the heart or lungs lead to failure to maintain adequate blood oxygen levels and/or increased blood carbon dioxide levels [1]. It is caused by a number of common cardiac or respiratory diseases, including heart failure, pneumonia, and exacerbations of chronic obstructive pulmonary disease (COPD) and asthma [2]. There are approximately 3000 ARF cases in England per year, with a high 14% risk of death within 30 days [3]. ARF has substantial health services costs, with patients often requiring prolonged hospital stays, ventilatory support and critical care admissions [4]. ARF was responsible for over 3 million National Health Service (NHS) bed days in England in 2014 [5].

Current prehospital clinical practice guidelines recommend a standard management approach of oxygen therapy for the treatment of acute respiratory failure, supplemented by specific management options directed at the underlying disease [6–8]. Prehospital administration of continuous positive airway pressure (CPAP) may be a potentially beneficial alternative treatment strategy [9]. CPAP involves delivering oxygen-enriched air to the lungs at increased pressure through a close-fitting face mask and is widely used in hospital to treat ARF from a number of causes [10]. It has been suggested that CPAP may be more effective if delivered earlier, i.e. en route to hospital [11]. The difficulties of prehospital diagnosis mean that prehospital CPAP is likely to be applied generally to all cases of acute respiratory failure, rather than directed towards those due to a specific cause [12].

A recent evidence synthesis reported that prehospital CPAP reduced the risk of mortality and requirement for endotracheal intubation in ARF compared to standard treatment but noted that the primary studies were relatively small, heterogeneous, at risk of bias and may not be applicable to the NHS [3, 9]. A recent economic evaluation suggested that prehospital CPAP was more effective than standard care but was also more expensive, with an incremental cost-effectiveness ratio of £20,514/quality-adjusted life year (QALY) and a 49.5% probability of being cost-effective at the £20,000/QALY threshold. Expected value of perfect information (EVPI) analyses suggested that further research costing up to £22.5 million could represent value for money, while expected value of sample information (EVSI) analyses suggested that a randomised trial recruiting 1000 patients per arm would be cost-effective if research costs were less than £18.1 million. However, these cost-effectiveness results were predicated on the accuracy of published effectiveness data and were very sensitive to estimates for the incidence of acute respiratory failure.

Taken together, these findings suggest that although prehospital CPAP is a promising therapy, further research is needed to examine whether the reported clinical and cost-effectiveness are confirmed in the UK setting. Prior to a large pragmatic trial and economic evaluation comparing prehospital CPAP to standard care, it is first necessary to estimate the incidence of eligible patients and to assess whether a trial would be feasible and cost-effective. We also need to determine whether prehospital CPAP can be delivered in the context of the NHS ambulance service. Prehospital trials need to overcome a number of potential practical barriers if they are to deliver valid data. For these reasons, a stand-alone feasibility study is necessary to estimate the incidence of eligible patients and test the feasibility and acceptability of potential definitive trial methods.

## Methods

### Study design, aims and objectives

The ACUTE study is a stand-alone, randomised, parallel group, external pilot trial. A concurrent health economic evaluation will also be performed, updating an existing decision analytic model [3]. The study aims to determine the feasibility, acceptability and cost-effectiveness of a definitive trial to evaluate the clinical and cost-effectiveness of prehospital CPAP compared to standard oxygen therapy, for patients attended by ambulance service clinicians with ARF. The study design is summarised in Fig. 1 and the schedule of enrolment, interventions and assessments summarised in Table 1.

**Fig. 1 Fig1:**
[figure not shown]
Flowchart of participants through the ACUTE study [CONSORT diagram]

**Table 1 Tab1:** Schedule of enrolment, interventions and assessments

	Study period						
	Enrolment	Allocation	Post-allocation				
Time point	0–5 min	5–10 min	10–60 min	1–5 h	1–29 days	30 days	30–37 days
Enrolment							
Eligibility screen	X						
Informed consent	X				X		
Allocation		X					
Interventions							
CPAP			X				
Standard oxygen therapy			X				
Assessments							
Patient characteristics	X	X	X				
ED physiology and treatments				X			
Hospital treatments					X		
Clinical outcomes						X	
Quality of life and health resource use							X

The primary objectives are to estimate the following feasibility outcomes:The rate of eligible patients per 100,000 population per yearThe proportion recruited and allocated to treatment appropriatelyAdherence to allocated treatmentRetention and data completeness up to 30 daysExpected net benefit of sampling for a range of study sizes to identify the optimal definitive trial design

Secondary objectives are to estimate the following summary clinical outcome measures, across the whole trial population and per treatment group:Proportion surviving to 30 daysProportion undergoing endotracheal intubation by 30 daysProportion admitted to critical care at any point up to 30 daysMean and median length of hospital stayChange in visual analogue scale (VAS) dyspnoea score from presentation to immediately before ED arrivalMean change in quality of life, measured with EQ-5D-5LKey elements of health care resource use up to 30 days

This clinical data will be used to update an existing network meta-analysis and economic model, [3, 9] to determine the cost-effectiveness of prehospital CPAP given current evidence. The summary clinical outcome measures will also inform the design of any future definitive trial.

### Setting and study population

The study will take place in the West Midlands Ambulance Service (WMAS), which serves a mixed urban and rural population of 5.6 million. It employs approximately 4000 staff across five divisions and operates from 15 ‘super-hubs’, each covering five to ten community ambulance stations. Recruitment will take place across four super-hubs in two divisions covering a population of 1.5 million. Included hubs were chosen to provide a representative mixture of urban, semi-urban and rural localities.

The study population will comprise adults transported to hospital by emergency ambulance with ARF. Inclusion and exclusion criteria will be based on ambulance service clinician judgement at the scene of incident. Acute respiratory failure will be defined as respiratory distress with peripheral oxygen saturation below British Thoracic Society (BTS) target levels (88% for patients with COPD, 94% for other conditions), despite supplemental oxygen (titrated low flow oxygen for COPD, or titrated high flow oxygen in other conditions) [13].

Potential participants will be excluded if any of the following criteria are met:Hospital CPAP treatment available within 15 min of eligibility assessmentAge < 18 yearsKnown to have terminal illnessKnown pre-existing lack of capacity (confirmed by relatives, carers or documentary evidence, such as lasting power of attorney)Documented not for resuscitation statusAcutely incapacitated patients with known valid advanced directive declining non-invasive ventilation or participation in researchThe patient has an oxygen alert cardAnticipated inability to apply CPAP (e.g. facial deformity)Respiratory failure due to chest traumaContraindication to CPAP (suspected pneumothorax, respiratory arrest, epistaxis, vomiting, hypotension)Previous enrolment in the ACUTE trialPregnancyPatients unable to communicate with ambulance service clinicians

### Randomisation, allocation concealment and participant enrolment

Patients presenting to ambulance service clinicians with ARF will be individually randomised to CPAP or standard oxygen therapy in a 1:1 ratio using simple, unrestricted randomisation. The randomisation sequence will be computer-generated by an independent statistician who is not directly involved in the conduct of the trial. The allocation sequence will be held centrally on a password-protected, access-restricted network drive. The trial statistician will not have access to the randomisation sequence until after data lock. Due to the physical differences between the CPAP device and standard oxygen mask, it is not possible to blind patients, ambulance service clinicians or hospital clinicians to the treatment arms. Outcome assessors will also not be blinded. However, both primary and secondary endpoints comprise ‘hard’ objective measurements, minimising the possibility of information bias.

CPAP devices (intervention arm) and high-concentration oxygen therapy masks (control arm) will be packaged in identical equipment boxes measuring approximately 170 mm × 170 mm × 70 mm. The boxes will be tamper-proof and equal in weight and appearance to maintain allocation concealment. Boxes can only be opened after a patient is definitively enrolled in the trial. Once a box is opened when attending a patient, that patient will be included in the study as per allocated treatment. It will not be possible to re-seal the box. Equipment boxes will be assembled, numbered and sealed in accordance with the allocation sequence by researchers not directly involved in the conduct of the trial, under the supervision of the trial manager. Boxes will then be transferred to the central WMAS storage and distribution centre where they will be held in an access-restricted research store. Boxes will subsequently be supplied to participating ambulance hubs as required by the WMAS internal distribution team and held locally in a designated storage area. Ambulance service clinicians will then collect an equipment box at the beginning of each shift. At the end of the shift, boxes will be returned to the ambulance hub equipment store. Boxes will be signed in and out for each shift with ambulance service clinician, ambulance and equipment box details recorded in a distribution log. Research paramedics will monitor the condition, status and location of boxes on a weekly basis to ensure concealment of the allocation sequence until treatment assignment occurs.

Ambulance service clinicians (paramedics, ambulance technicians, paramedic practitioners or critical care paramedics) will identify patients with ARF when attending 999 ambulance calls. Patients meeting trial inclusion criteria will be approached for enrolment in the trial guided by a standardised script. If possible, verbal consent will be obtained for participation prior to enrolment. Patients lacking capacity will be enrolled according to a hierarchical consent process complying with the Mental Capacity Act (MCA) 2005 [14] described below. Immediately after inclusion, ambulance service clinicians will open the trial equipment box and provide treatment according to whether a CPAP device or high-concentration oxygen mask is supplied.

### Consent

A hierarchical consent process will be used complying with the Mental Capacity Act (MCA) 2005 [14]. Verbal consent will be obtained for enrolment if the treating ambulance service clinician determines that the patient has capacity. Ambulance service clinicians will enrol patients without consent if the patient does not have capacity. In either case, a research paramedic will review the participant in hospital as soon as possible after enrolment, provide verbal and written information regarding the study and seek written informed consent as soon as the participant has capacity. If the patient does not regain capacity, we will seek advice from a personal consultee for enrolment in the trial [15]. When a personal consultee is unavailable, a nominated consultee will be approached for a consent waiver [15]. If patients (or their consultees) decline consent, all non-identifiable data up to the point of refusal will be retained. No further data collection will be conducted from this point onwards, except for anonymised 30-day mortality data.

### Trial treatments

Patients in the intervention arm will be treated by CPAP with supplemental oxygen. Patients in the control arm will receive standard oxygen therapy. Treatment in both arms will be targeted to BTS guidelines for peripheral oxygen saturations [13]. Ancillary condition-specific treatments will be administered in both trial arms according to standard practice guidelines [8]. Ambulance service clinicians (paramedics, ambulance technicians, paramedic practitioners or critical care paramedics) will deliver trial treatments.

#### Intervention arm

CPAP is a form of non-invasive ventilation (NIV) where oxygen or air is supplied to the upper airways at increased pressure [16]. The ACUTE trial will use the O_two unit, a lightweight, open, single-use, low-flow CPAP system [17]. The device consists of tubing, which is connected to an oxygen source (either a portable oxygen cylinder or the usual ambulance oxygen flow regulator), and an in-line CPAP unit connecting to a close-fitting face mask. The CPAP unit entrains ambient air to increase local mask pressure, providing resistance for the patient to breathe against. The level of CPAP is varied by altering the incoming oxygen flow rate. Thus, the inspired concentration of oxygen varies according to the desired degree of CPAP, as the flow rate is altered. As an open system, with access to ambient air, the device allows unrestricted inspiratory flows and is unaffected by respiratory rate.

Treatment may be commenced at the site of initial clinical contact or after transfer to an ambulance. An appropriately sized mask will be used, with CPAP started at 5 cm H_2_O and then incrementally increased by 1 cm H_2_O every 2–5 min to a maximum of 15 cm H_2_O according to BTS peripheral oxygen saturation targets [13] measured by standard pulse oximetry. Target peripheral oxygen saturations will be 88–92% for patients with known/suspected COPD and 94–98% for patients with other suspected causes of acute respiratory failure. If necessary, nebuliser treatments can be positioned between the face mask and the O_two CPAP unit. CPAP will be continued until arrival at hospital unless not tolerated (e.g. patient request, claustrophobia, anxiety, significant agitation); patient is unable to maintain own airway; decrease in systolic blood pressure to < 90 mmHg; vomiting; epistaxis; conscious level decreases and patient does not respond to voice; patient improvement; or suspected pneumothorax.

#### Control arm

Oxygen will be delivered at normal atmospheric pressure from a compressed gas tank (or portable oxygen cylinder), via a flow regulator, to the patient using nasal cannula, an air entrainment ‘Venturi’ mask, a simple face mask or a non-rebreathing reservoir face mask. The exact choice of flow rate and oxygen delivery device will be determined by ambulance service clinicians according to the patient’s condition and peripheral oxygen saturation levels. Target oxygen saturations will be 88–92% for patients with known or suspected COPD and 94–98% for other suspected causes of acute respiratory failure.

On arrival at hospital emergency department, staff will be informed of the study and current treatment. Patient care will then be transferred from ambulance service clinicians to hospital clinicians according to normal practice. Care will subsequently continue according to hospital guidelines as implemented by the hospital clinician. In the intervention group, the hospital clinician will determine whether to continue NIV using the O_two unit, switch to an in-hospital system or discontinue NIV altogether. Patients in the control group will be able to receive in-hospital NIV if indicated, according to assessment by the hospital clinician.

The West Midlands Ambulance Service (WMAS), O_two representatives and research paramedics will provide training and support for all ambulance service clinicians based at the participating ambulance hubs. This will involve training in identification of eligible patients, application of the inclusion/exclusion criteria, providing appropriate information and seeking consent, randomisation, delivery of CPAP, monitoring for adverse events (AEs) and data collection. Training will specifically focus on study exclusion criteria, particularly the identification of clinical conditions, e.g. pneumothorax or vomiting, where administration of CPAP could be harmful. Training strategies will include online training modules, small group teaching, demonstration, hands-on familiarisation and scenario-based practice. Only once an ambulance service clinician has received this training and has been assessed to be competent will they be permitted to enrol patients into the trial. Research paramedics will provide ongoing support and training as necessary, including training of new ambulance service clinicians starting at ambulance hubs after recruitment to the study has begun.

### Data collection

A recruitment form (case report form (CRF) A), contained within each equipment box, will be completed every time a patient is enrolled in the trial. This will record study number, basic demographic details, eligibility criteria, suspected prehospital diagnosis,, consent details and limited clinical and treatment data not routinely recorded, including a patient and ambulance service clinician completed VAS dyspnoea scale (1–10) recorded on initial assessment and immediately before ED arrival. Routinely collected baseline characteristics, EMS timings, details of treatments provided and vital signs (including peripheral oxygen saturations) en route to hospital will be extracted from the ambulance service patient report forms/electronic patient records into ACUTE case report form B (CRF B) by research paramedics. At 30 days, research paramedics will also review the hospital records to record details of subsequent progress, treatments provided (including time to receiving hospital NIV, if provided), length of hospital stay, use of critical care, any adverse events (AEs) and status at 30 days. Any related AEs or serious AEs will be recorded on the study case report form (CRF B).

Baseline quality of life assessments will be performed by research paramedics shortly after hospital admission, following confirmation of patient consent for participation in the trial. Patients, or their representatives, will be asked to estimate their current health status, using the EQ-5D-5L. This data will be recorded in the study case report form (CRF B). Quality of life and resource use will also be assessed remotely by questionnaire at 30 days following enrolment. Participants will be asked for their preferred method for data collection, either telephone or postal. Initial non-responders will be contacted again after a further 2 weeks by telephone or post. Key elements of health care resource use to be recorded will include hospital services and GP or community services. Participants will also be asked to report any AEs in the 30-day follow-up questionnaire. For patients’ declining consent for follow-up, anonymised 30-day mortality will be recorded. The assessments and follow-up for the ACUTE trial are summarised in Table 2.

**Table 2 Tab2:** Summary of data collection and trial documentation

What	Where	Who	How		When	
				Baseline	Hospital admission	30 days
Consent form						
•Verbal consent	Scene of incident	Paramedics	Verbal	X		
•Written informed consent	Hospital	Research paramedic	Paper		X	
Case report form A						
•Patient demographics	Scene of incident/emergency department	Paramedics	Paper	X		
•Patient characteristics			Telephone	X		
•Prehospital treatments •Adverse events				X X		
Case report form B						
•Patient demographics	Hospital	Research paramedic	Paper		X	
•Baseline quality of life					X	
•Inpatient treatments						X
•30-day mortality						X
•Intubation						X
•Critical care admission						X
•Length of stay •Adverse events					X	X
Patient questionnaire						
•Quality of life	Home	Patient	Paper			X
•Resource use		Research paramedic	Telephone			X
•Adverse events						X
Paramedic questionnaire						
•Acceptability of CPAP	Home/work	Paramedics	Electronic	X		
HRA safety report form						
•Unexpected related serious adverse events	CTRU	Chief investigator	Electronic	X	X	X
SAE form						
•Other serious adverse events	CTRU	Chief investigator	Paper	X	X	X

*CTRU* clinical trials and research unit, *SAE* serious adverse event, *CPAP* continuous positive airways pressure

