### Data management

All data will be collected and retained in accordance with the UK Data Protection Act 1998 and University of Sheffield clinical trials and research unit (CTRU) standard operating procedures (SOPs). Trial data will be extracted from source documents and CRFs and entered onto a secure data management system. Patient identifiable data (names, date of birth and contact details) will only be collected and entered on the prospect database when written informed consent has been confirmed. Validation reports will be run regularly to check the study data for completeness, accuracy and consistency. Discrepancies will be generated, monitored and managed by research paramedics to resolution.

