### Sample size and statistical analyses

Participant recruitment and retention will be presented with a CONSORT flow diagram [18]. The following feasibility outcomes will then be reported descriptively for the whole trial population, together with their 95% confidence interval (calculated using the Wilson score method) [19]:Recruitment rate per 100,000 population per year (target 8, i.e. 120 across the 1.5 million population of the 4 WMAS hubs)Proportion recruited in error and classified as minor or major non-compliances (target 0 and ≤ %)Adherence to the allocation schedule (target ≥ 90%)Adherence to treatment in the CPAP arm (target ≥ 75%)Retention at 30 days (target ≥ 90%)Data completeness (target ≥ 90%)

Summary estimates of effectiveness outcomes will also be reported, for the whole trial population and separately per treatment group, with 95% confidence intervals using an as-randomised analysis:Proportion surviving to 30 daysProportion undergoing endotracheal intubation by 30 daysProportion admitted to critical care at any point up to 30 daysMean and median length of hospital stayChange in VAS dyspnoea score from initial presentation versus immediately before ED arrivalMean EQ-5D-5LKey elements of health care resource use up to 30 days

The ACUTE feasibility study aims to recruit *n* = 120 over 12 months. A minimum sample size of 120 was proposed by Teare et al. for pilot studies with dichotomous outcomes, based on the precision to which binary parameters are estimated for use in the sample size calculation of the full trial [20]. Mortality under standard care is estimated at 12%, and for the full trial, a 5% absolute reduction is postulated (i.e. to 7%) in the intervention arm. With *n* = 120, we will therefore be estimated to within a standard error of 2.7% and used in the sample size calculation for the eventual trial. Given the short follow-up period, loss to follow-up of < 5% at 30 days is envisaged. This sample size will allow estimation of feasibility outcomes with a precision of < 5%.

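### The only named source for 30-day survival, the intended definitive primary endpoint, is a review of hospital records, which need not show deaths after discharge

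*Protocol article*

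**What the plan says.** The abstract's Methods paragraph names the key outcome as "survival at 30 days (definitive trial primary end point"). The section Data collection states how it is obtained: "At 30 days, research paramedics will also review the hospital records to record details of subsequent progress, treatments provided", and the list of items continues with "length of hospital stay, use of critical care, any adverse events (AEs) and status at 30 days". Table 2 agrees: "30-day mortality" is an item on case report form B, a block whose location is given as hospital and which a research paramedic completes on paper.

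There is a second contact at day 30: "Quality of life and resource use will also be assessed remotely by questionnaire at 30 days following enrolment". Initial non-responders are contacted once more after two weeks. Data collection and Table 2 give the questionnaire three purposes: quality of life, resource use and adverse events. Vital status is not among them.

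For patients who decline follow-up, "anonymised 30-day mortality will be recorded"; the source is not stated. Under Data management, names, dates of birth and contact details "will only be collected and entered on the prospect database when written informed consent has been confirmed".

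Under Sample size and statistical analyses, retention at 30 days has a target of at least 90%, and loss to follow-up below 5% is expected. The article does not define retention.

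**The concern.** The endpoint runs to day 30 from enrolment, whereas a hospital record follows the patient's contact with the hospital. Take a patient discharged on day 5 who dies at home on day 20. The reviewed record may show only a live discharge. Some hospital systems do pick up outside deaths, but nothing in the article requires or checks this.

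The questionnaire does not close the gap. A patient who has died becomes a non-responder, and a second unanswered contact does not distinguish death from ordinary non-response. Patients who decline follow-up do not have even this safeguard.

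A missed death can only push observed mortality down. The pilot's mortality is to be used in sizing the definitive trial, and the pilot is meant to show that the definitive trial's methods work, including ascertainment of its primary endpoint. In the section on randomisation and enrolment, the article also relies on its endpoints being hard and objective to justify unblinded outcome assessment. Death is an objective endpoint, but that helps only when the death is found.

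**Working it through.** **Inputs from the article.** Mortality is 12% under standard care and 7% with CPAP; allocation is 1:1; the pilot has 120 patients (Sample size and statistical analyses; Randomisation). The definitive trial is planned with 90% power, two-sided 5% significance, 5% attrition and N = 1518 (Discussion).

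**Input not in the article.** f is the share of 30-day deaths that are missed and read as survival. I assume 10% to 30%, equal in both arms.

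**Step 1: reproduce the article's figures.**
- Pooled mortality: (12% + 7%)/2 = 9.5%. Standard error: √(0.095 × 0.905/120) = 2.68%, which matches the stated 2.7%.
- Definitive trial, pooled null variance, no continuity correction: n per arm = [1.960√(2 × 0.095 × 0.905) + 1.282√(0.12 × 0.88 + 0.07 × 0.93)]² / 0.05² = 721 after rounding up. Then 721/0.95 rounds up to 759 per arm, and 2 × 759 = 1518, an exact match.

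The article's arithmetic is not in question. What follows is a sensitivity calculation.

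**Step 2: effect on the pilot.** Expected deaths are 120 × 0.095 = 11.4. Deaths missed are 11.4f. Observed pooled mortality is 9.5% × (1 − f), and observed control mortality is 12% × (1 − f).

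| f | Deaths missed | Pooled mortality read as | Control mortality read as |
|---|---|---|---|
| 0% | 0 | 9.5% | 12.0% |
| 10% | 1.1 | 8.55% | 10.8% |
| 20% | 2.3 | 7.6% | 9.6% |
| 30% | 3.4 | 6.65% | 8.4% |

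At f = 30% the downward shift is 9.5 − 6.65 = 2.85 points, slightly more than the 2.7% standard error cited in support of the pilot's size.

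**Step 3: effect on the treatment contrast.** With equal missing, the risk ratio is unchanged: 7/12 = 6.3/10.8 = 4.9/8.4 = 0.583. The odds ratio hardly moves:
- f = 0: (0.07/0.93)/(0.12/0.88) = 0.552
- f = 10%: (0.063/0.937)/(0.108/0.892) = 0.555
- f = 30%: (0.049/0.951)/(0.084/0.916) = 0.562

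**Step 4: effect on the definitive trial, conditional on further assumptions.**
- If the planners kept a 5-point absolute effect but started from the understated control rate, the Step 1 formula would give N = 1344, 1166 and 980 for f = 10%, 20% and 30%, instead of 1518.
- If the definitive trial kept both this ascertainment and N = 1518 (721 evaluable per arm), power would be 86.4%, 81.8% and 76.1% instead of 90%.

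**The case against.** The best counter-argument is that this is a condensed article. The full protocol may name a further source of vital status, a coding rule for unknown status and a definition of retention, and their absence here is not an error. The text also asks for status at 30 days, listed separately from length of stay, and not for status at discharge. The hospital entry in Table 2 covers the whole of case report form B and may only say where the form is completed. Repeat contact with non-responders, the serious adverse event form and the validation reports could each reveal some deaths. The 10% to 30% range has no source. Even at its upper end, the shift lies within the roughly ±5 points (1.96 × 2.68) of sampling error in a pilot that is reported descriptively.

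Most of this stands as a limit on the claim. It does not remove the point, because the article is not silent: it names the source, the person and the time of the review. A team following it exactly could miss deaths after discharge, and none of the other routes is assigned to vital status. Sampling error is shown by the confidence interval; a one-directional ascertainment error is not.

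Three stronger readings are tempting and are not supported:
- *Patients discharged alive are counted as 30-day survivors, or as retained.* No section says so, and the expected loss to follow-up of under 5% shows that some unknown outcomes are foreseen. The article merely does not rule it out.
- *Recording mortality for decliners contradicts the limit on identifiers.* It does not. That limit concerns data entered on the trial database, and a look-up reported anonymously is compatible with it.
- *The meta-analysis and economic model would receive a biased effect.* The model works from odds ratios, and Step 3 shows that equal missing leaves the odds ratio almost unchanged.

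**Conclusion.** The point holds as a weakness in how the intended definitive primary endpoint is ascertained. The one named source need not show deaths after discharge, so 30-day mortality can be understated.

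The size cannot be derived from the article. With 10% to 30% of deaths missed, about 1 to 3 of 11.4 expected deaths would be lost, and pooled mortality would read about 8.6% to 6.7% instead of 9.5%. What is at risk is the event rate used for sizing, not the relative effect, provided that missing is equal in both arms. The figures for planned N and power in Step 4 carry further assumptions about a trial whose methods are not yet fixed, and should be read as illustrations only. The change is worth making because it is cheap and the stated method is clearly improvable, not because a bias of known size has been shown.

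**What to change.** In Data collection and in Table 2:
- Have the research paramedic confirm vital status on or after day 30 for every randomised patient, from a source that covers deaths outside hospital, for example the NHS or GP record. Report it anonymously for patients who decline follow-up.
- Record the source and the date of the check on case report form B.
- Treat unconfirmed status as missing, not as alive. This makes any remaining gap visible; the check itself is what closes it.

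Under Sample size and statistical analyses, count a patient as retained for the survival endpoint only when status at day 30 is confirmed.

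The cost is about 120 look-ups, two form fields, a wording change and possibly a minor ethics notification. The reported retention figure may be slightly less favourable.
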